## Abstract

**Background:**

The midwifery continuity of care model is one of the care models that have not been evaluated well in some countries including Iran. We aimed to assess the effect of a program based on this model on the clinical competence of midwifery students and delivery outcomes in Ahvaz, Iran.

**Methods:**

This sequential embedded mixed-methods study will include a quantitative and a qualitative phase. In the first stage, based on the Iranian midwifery curriculum and review of seminal midwifery texts, a questionnaire will be developed to assess midwifery students’ clinical competence. Then, in the second stage, the quantitative phase (randomized clinical trial) will be conducted to see the effect of continuity of care provided by students on maternal and neonatal outcomes. In the third stage, a qualitative study (conventional content analysis) will be carried out to investigate the students’ and mothers’ perception of continuity of care. Finally, the results of the quantitative and qualitative phases will be integrated.

**Discussion:**

According to the nature of the study, the findings of this research can be effectively used in providing conventional midwifery services in public centers and in midwifery education.

**Trial registration:**

This study was approved by the Ethics Committee of Ahvaz Jundishapur University of Medical Sciences (IR.AJUMS.REC.1401.460). Also, the study protocol was registered in the Iranian Registry for Randomized Controlled Trials (IRCT20221227056938N1).

## Background

Providing quality services to pregnant women has been recommended to all countries to achieve the Millennium Development Goals (MDGs) (Goals 3, 4 and 5) [1]. There are different care methods to maintain maternal and neonatal health during pregnancy and postpartum [1]. One of these care models is continuity of care that can be provided by a midwife or an obstetrician.

Midwifery continuity of care is a relationship-based care provided by a midwife who can be supported by one to three more midwives. They provide planned care for a woman during pregnancy, labor, birth, and the early postpartum period up to 6 weeks after delivery [2].

Continuity of midwifery care has become a global effort to enable women to have access to high-quality maternity care and delivery services [3]. As a result, many service providers today are transitioning to a continuous care model [4], and they have considered continuous care to be necessary for realizing women's rights [5]. Also, continuous midwifery care is known as the gold standard in maternity care to achieve excellent results for women [5, 6]. In order to strengthen midwifery services to achieve global health goals in 2015, the World Health Organization (WHO) proposed a midwife-led continuous care model [7].

Countries use different midwifery care models. In Iran, for example, primary health services that are specific to pregnant mothers are provided in public health centers by midwives working in the network system and in compliance with the level of services and the referral system [8].

In general, midwifery continuous care not only has an important impact on a wide range of health and clinical outcomes for mothers and neonates but also brings about economic consequences for the health system [2, 9]. This care model is useful for healthcare professionals as well [10], and it has improved the job satisfaction of midwives [11]. The midwife is the main guide in planning, organizing and providing care to a woman from the beginning of pregnancy to the postpartum period [12]. In 2011, in order to increase job motivation and satisfaction, promote retention of the midwifery workforce [13], and alleviate the shortage of workforce at the international level [14], the Nursing and Midwifery Advisory Center recommended using midwifery students (at the bedside and to perform midwifery work) to overcome this problem.

Providing high quality care requires enhancing the clinical competence of the professionals [4]. There is a close relationship between the concept of patient care quality and clinical competence. Therefore, clinical competence is of unique importance in midwifery practice [15]. As a result, in order to achieve quality patient care, midwifery professionals need to train students to become workforce with clinical competence in order to provide quality care in the health system. WHO defined clinical competence as a level of performance that demonstrates the effective application of knowledge, skills, and judgment [16].

A previous study showed that clinical competence of midwives plays an important role in managing the process of providing care, achieving care goals, and improving the quality of midwifery services [17]. In other words, the graduates of this field must have an acceptable level of clinical and professional skills in performing midwifery duties so that the health of mothers, children, and ultimately the community can be improved.

In Iran, prenatal care and the care during labor, delivery and postpartum are not continuous, and a new health provider may take the responsibility of care at any stage. This fragmented care may negatively affect the pregnancy outcomes and increase the rate of cesarean section [18]. Furthermore, the results of some studies in Iran indicate that the clinical competence obtained by midwifery students is far from optimal and that they do not acquire the necessary skills and abilities at the end of their studies [19]. Farrokhi et al. showed that the performance quality of 70% of midwives is average, and only 18.5% of them have good quality performance [20]. Several factors play a role in acquiring, maintaining and improving clinical competence [21]. There are a number of solutions that can increase the clinical competence of midwifery students, and one is the use of different care models such as the continuity of care model. The continuity of care model allows students to develop their midwifery knowledge, skills, and values individually [22]. Despite the strong foundation of midwifery in Iran, midwifery care models have not yet been tested. Some studies have reported that the quality of services provided during pregnancy, delivery and after delivery in Iran is poor to moderate. Also, these studies emphasize the necessity of a paradigm shift for better quality care and greater satisfaction of mothers, and they consider lack of continuity of care as the reason for the increase in unnecessary cesarean sections [23–25]. Moreover, the lack of qualified and experienced workforce has led to low quality health services, including midwifery care, and an increase in the economic burden of health. In Iran, no study has yet been conducted to investigate the effect of the midwifery continuity of care model on the students’ clinical competence and pregnancy outcomes. Given the importance of this topic, using a mixed-methods study design, we aimed to assess the effect of a midwifery continuity of care program on the clinical competence of midwifery students and pregnancy outcomes in Ahvaz, Iran.

### Specific objectives

To determine the effect of midwifery continuity of care program on the clinical competence of midwifery students.To determine the effect of a midwifery continuity of care program provided by midwifery students on pregnancy outcomes.To explain the perception of midwifery students and mothers about the use of the midwifery continuity of care program provided by midwifery students.

## Methods/design

### Study design

This sequential embedded mixed-methods study will include a quantitative phase and a qualitative one. A mixed (embedded) experimental design involves the collection and analysis of quantitative and qualitative data by the researcher and the integration of the information into an experimental study or intervention trial. This design adds qualitative data to an experiment or intervention to integrate the personal experience of research participants. Therefore, the qualitative data are converted into a secondary source of data embedded before and after the test. Qualitative data is added to the experiment in differrent ways, including: before the experiment, during the experiment, or after the experiment [26, 27]. Embedded mixed-methods studies that are qualitative followed by quantitative are used to understand the rationale for the results and receive feedback from participants (to confirm and support the findings of the quantitative studies) [27]. In the first stage of this study, a questionnaire for assessing midwifery students’ clinical competence will be created based on the midwifery curriculum of Iran and a review of seminal texts of midwifery. Then, the effect of continuity of care provided by midwifery students on maternal and neonatal outcomes will be assessed in a randomized clinical trial. In the third stage, a qualitative study will be carried out to investigate the perception of students and mothers. Finally, the results of the quantitative and qualitative phases will be integrated (Fig. 1).

**Fig. 1 Fig1:**

Sequential and embedded mixed-methods design

### First stage: questionnaire development

This questionnaire will be developed based on midwifery curriculum and a comprehensive and systematic search (with no time limit) in English and Persian databases (Web of Science, Embase, Scopus, ProQuest, Google scholar, Magiran, SID).

### Tool design

There are four steps in tool development:Choosing a conceptual model to show aspects of clinical competence in the measurement processExplaining the purpose of the toolDesigning the route mapDeveloping the tool (use of methods, classification of objects, rules and procedures for scoring tools) [28].

### Answer to the objects

A 1 to 4-point Likert scale will be used for scoring [29].

### Content validity

To ensure the selection of the most important and correct content (necessity of the case), the content validity will be assessed. Also, to ensure that the instrument items are designed in the best way to measure the content, the content validity index will be calculated [30].

### Reliability

Reliability will be evaluated using internal consistency (Cronbach's alpha coefficient ≥ 0.7) and stability (test-re-test ≥ 0.74) by piloting the questionnaire on 20 midwifery students [31].

### Second stage: quantitative phase

A randomized controlled clinical trial will be conducted in this phase of research to examine the effect of the continuous care program of midwifery students on their clinical competence and pregnancy outcomes.

### Sample size

According to the study objective and previous study results [32] with α = 0.01, β = 0.1, p_1_ = 0.51 and p_2_ = 0.021, the sample size will be *n* = 23. Considering a 20% dropout rate, the final sample size will be 58 women (29 women in each group).$$\begin{array}{l}n=\frac{{\left({z}_{1-\alpha /2}+{z}_{1-\beta }\right)}^{2}*\left[{p}_{1}\left(1-{p}_{1}\right)+{p}_{2}\left(1-{p}_{2}\right)\right]}{\left({p}_{1-}{p}_{2}\right)^{2}}\\ \mathrm{Z}_{1-\mathrm{\alpha }/2}=2.57\\ \begin{array}{l}\mathrm{Z}_{1-{\mathrm\upbeta} }=1.28\\ {\left(2.57+1.28\right)}^{2}*\left(0.55\left(0.45\right)+0.021\left(0.979\right)\right)/{\left(0.529\right)}^{2}=23\end{array}\end{array}$$

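### The 23 per group does not follow from the printed sample-size formula, and the substitution uses p1 = 0.55 where the text states 0.51

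*Protocol article*

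**What the plan says.** The Sample size section of the protocol article sets the error rates "with α = 0.01, β = 0.1" and gives the two proportions and the result as "p_1_ = 0.51 and p_2_ = 0.021, the sample size will be *n* = 23". It attributes these inputs to a previous study and does not say which outcome the proportions describe.

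It then prints the two-proportion formula with unpooled variances and z-values of 2.57 and 1.28. The final line multiplies the squared sum of the z-values by "0.55\left(0.45\right)+0.021\left(0.979\right)\right)/{\left(0.529\right)}^{2}=23".

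The last step is "Considering a 20% dropout rate", after which "the final sample size will be 58 women (29 women in each group"). The Data collection section under the second stage uses 58 both for the women and for the students.

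**The concern.** Two things are wrong within one paragraph. First, the assumed rate changes: the sentence says 0.51, but the substitution uses 0.55. Second, the substituted line looks too small to equal 23.

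This calculation is the only support in the article for the trial's size and for its claim of 90% power at α = 0.01. If 23 does not come from the stated inputs, neither do 29 per group and 58 in total. A reader then cannot tell which rate was assumed, which formula was used, or what power the trial has.

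**Working it through.** **Inputs, all from the Sample size section**

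| Input | Value |
|---|---|
| α (two-sided, since the formula uses z at 1 − α/2) | 0.01, printed z = 2.57 |
| β | 0.1, printed z = 1.28 |
| p1 in the sentence | 0.51 |
| p1 in the substitution | 0.55 (complement 0.45, difference 0.529) |
| p2 in both places | 0.021 |
| Dropout | 20% |

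**Which p1 was used?** With p1 = 0.51 the complement would be 0.49 and the difference 0.51 − 0.021 = 0.489. The printed numbers are 0.55, 0.45 and 0.529 = 0.55 − 0.021. All three agree with 0.55 and none with 0.51, so a single misread digit does not explain the conflict.

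**The plan's own line.** The formula is n = (z₁ + z₂)² × [p1(1 − p1) + p2(1 − p2)] / (p1 − p2)².

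- (2.57 + 1.28)² = 3.85² = 14.8225
- 0.55 × 0.45 + 0.021 × 0.979 = 0.2475 + 0.020559 = 0.268059
- 0.529² = 0.279841
- n = 14.8225 × 0.268059 / 0.279841 = **14.20**, so 15 per group

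**The same formula with the stated p1 = 0.51**

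- 0.51 × 0.49 + 0.020559 = 0.2499 + 0.020559 = 0.270459
- 0.489² = 0.239121
- n = 14.8225 × 0.270459 / 0.239121 = **16.77**, so 17 per group

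Unrounded z-values change these only to 14.25 and 16.83. The printed 23 is 62% above 14.2 and 37% above 16.8, so rounding is not the cause.

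**Dropout step.** 23 / 0.8 = 28.75, so 29 per group and 58 in total. This step is right and passes the unsupported 23 forward. From the printed formula it would be 15 / 0.8 = 18.75, so 19 per group (38 in total), or 17 / 0.8 = 21.25, so 22 per group (44 in total).

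**Could 23 come from another formula?** At two-sided α = 0.01 and 90% power:

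| Formula | p1 = 0.51 | p1 = 0.55 |
|---|---|---|
| Unpooled (as printed) | 17 | 15 |
| Arcsine | 18 | 16 |
| Pooled variance, no correction | 22 | 20 |
| Pooled variance, continuity-corrected | 26 | **23** |

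Only the continuity-corrected formula reaches 23, and only at 0.55. It is not the formula printed.

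**Power at 23 completers per group, two-sided α = 0.01**

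For the printed approximation, power = Φ[(p1 − p2)√n / √(p1(1 − p1) + p2(1 − p2)) − 2.57].

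- p1 = 0.51: 0.489 × 4.796 / 0.5201 − 2.57 = 1.94, so 97%
- p1 = 0.55: 0.529 × 4.796 / 0.5177 − 2.57 = 2.33, so 99%

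| Method | p1 = 0.51 | p1 = 0.55 |
|---|---|---|
| Printed unpooled approximation | 97% | 99% |
| Pooled-variance approximation | 92% | 96% |
| Exact binomial enumeration, Pearson chi-square | 96.8% | 98.4% |
| Exact binomial enumeration, Fisher exact test | 93.5% | 96.6% |
| Exact binomial enumeration, Yates-corrected chi-square | 89.4% | 94.3% |

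**The case against.** The best defence is that the error does no harm. The figure of 23 exceeds what the printed formula needs under either p1, and the dropout step is correct. A standard continuity-corrected formula gives exactly 23 at p1 = 0.55, so software output may simply have been set beside the wrong formula. On that reading 58 has a sound basis and only the typesetting is at fault.

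Much of this stands. The trial is not made too small by its own formula, and 58 may have a legitimate origin. The totals of 38 and 44 should not be read as the right size for the trial. With p2 = 0.021, only about 23 × 0.021 = 0.5 events are expected in that group, where the unpooled approximation is optimistic. At 17 per group with p1 = 0.51, exact power is about 85% (Pearson) or 74% (Fisher). At 15 per group with p1 = 0.55 it is about 84% or 71%. For the same reason, 97% to 99% is the output of the printed approximation and not the power of whichever test is finally run.

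The defence does not rescue the paragraph. The article does not print or mention the continuity-corrected formula, so that route is inference. If that formula was used, the displayed formula is wrong, and so is either the stated p1 or the n, because it gives 26 at 0.51. Nor is this a matter of an article condensing a fuller protocol: the whole calculation is shown, and what is shown is false.

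**Conclusion.** The concern holds. The printed equality is wrong: the expression equals 14.2, or 16.8 with the p1 that the text states, and not 23. The assumed rate also differs within the paragraph, 0.51 against 0.55. The 29 per group and 58 in total therefore do not follow from the stated α, β, p1 and p2.

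By the printed formula, the discrepancy is 8 per group (23 against 15) or 6 per group (23 against 17) before dropout. In total it is 20 or 14 women after dropout (58 against 38 or 44). It is on the generous side by that formula. It would be on the short side if p1 = 0.51 and the continuity-corrected formula were intended (23 against 26). The article does not settle which applies, and which p1 is right cannot be decided without the cited study.

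This is an error of traceability rather than a demonstrated loss of power. It should still be corrected, because no other support for the trial's size is given.

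**What to change.** Rewrite the Sample size paragraph so that it:

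1. gives one value of p1, taken from the cited previous study, in both the sentence and the substitution, and names the outcome to which p1 and p2 refer;
2. prints the formula or software procedure actually used, including any continuity correction, with a result that follows from it;
3. restates n, or keeps 58 and states the power that 23 completers per group gives, naming the test and p1 behind that figure.

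If the continuity-corrected formula with p1 = 0.55 was the source, saying so and correcting 0.51 would make 23, 29 and 58 all consistent. If p1 is 0.51, that formula gives 26, so 23 should be described as the planned number of completers with its own power.

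The cost is the rewording of one paragraph. Enrolment need not change.

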### Data collection

This phase of the randomized clinical trial will be conducted with the participation of 58 undergraduate midwifery students at their 7th and 8th semesters. The students will be divided randomly to intervention (continuous care) and control (routine care) groups providing care to 58 pregnant women in six health centers and two hospitals (Sina and Razi) in Ahvaz city, southwest of Iran.

The study will begin after receiving the approval of the Ethics Committee of Ahvaz University of Medical Sciences and registering the study in the Iranian Registry for Randomized Clinical Trials. Inclusion criteria will be willingness to participate in the study.

### Randomization

To implement the intervention, the students will be divided into two intervention (providing continuous care for pregnant women) and control (providing standard care for pregnant women) groups. Allocating students will be done using permuted block randomization technique with a block size of four and an allocation ratio of 1:1. Five blocks of 4 pieces and 3 blocks of 3 pieces will be extracted randomly using WIN PEPI software. In each block of 4, 2 students will be in control and 2 will be in intervention group. Also, in each block of 3 students, 1 student will be in control and 2 will be in intervention group, and the arrangement of each person is random. To prevent contamination, first the control group will provide routine care, and then the intervention group will conduct continuity of care for pregnant women. Mothers are randomly selected based on the hospital where they will give birth. As a result, Razi Hospital will be the control group and Sina Hospital will be the intervention group.

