### Follow-up

The students in the intervention group will start prenatal care < 20 weeks of gestation. At least five round of prenatal care will be provided by each student according to national guidelines for each pregnant woman. Pregnant women can communicate with their in-charge students in non-emergency cases from 8:00 a.m. to 23:00 p.m. and in emergency cases 24 h a day, all days a week. All reports will be recorded by the students. During labor and delivery, the student and the lead researcher will be present at the mother's bedside. In case of natural vaginal delivery (NVD), delivery will be done by a student midwife under the supervision of the researcher. In case of cesarean delivery (CS), a student will be present at the patient's bedside. Postpartum care will be provided by midwifery students in both groups (intervention and control). Each student will be at the mother's bedside for two hours after delivery. The conditions of labor, delivery, and the neonate will be recorded by the student in the relevant form. Also, the mother will be followed up by telephone for up to 6 weeks after delivery (postpartum). The clinical competency questionnaire will be completed by students before and after the intervention.

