### Inclusion criteria

Inclusion criteria for midwifery students will be: studying at the seventh and eighth semester and willingness to participate in the study.

Inclusion criteria for service recipients (pregnant women) will be: age 18 – 40 years, Iranian nationality, singleton pregnancy, low risk pregnancy, and gestational age < 20 wks.

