### Primary outcome

Clinical competence of midwifery students.

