### Inclusion criteria

Inclusion criteria for midwifery students will be: studying at the seventh or eighth semester, willingness to participate in the study.

Inclusion criteria for service recipients (pregnant women) will be: receiving continuous care provided by the student, willingness to participate in the study, and being able to communicate.

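### Allocation is not stratified by semester, a plausible prognostic factor for student competence that is known beforehand; stratifying, and adjusting for it, would improve balance and precision at almost no cost

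*Protocol article*

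**What the plan says.** In the quantitative phase, the Data collection section describes the randomised students as "58 undergraduate midwifery students at their 7th and 8th semesters". The Inclusion criteria for that phase repeat both semesters: "studying at the seventh and eighth semester and willingness to participate in the study". The Inclusion criteria for the qualitative phase join the two with a different word: "studying at the seventh or eighth semester, willingness to participate in the study". That wording supports reading the pool as a mix of students from two semesters.

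The Primary outcome section reads "Clinical competence of midwifery students". According to Follow-up, "The clinical competency questionnaire will be completed by students before and after the intervention", so a baseline score exists for each student.

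The Randomization section is fairly detailed. It states "Allocating students will be done using permuted block randomization technique with a block size of four and an allocation ratio of 1:1", then gives the number and size of the blocks, the split within each block and the software. It does not mention semester. The quantitative Data analysis section names the independent t-test for continuous outcomes and adds ANCOVA to deal with confounders, without naming any covariate.

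**The concern.** A student one semester further on has had more clinical training, and the trial measures clinical competence. Semester is therefore a plausible prognostic factor, and it is known before anyone is allocated. Blocks that ignore it balance the arms over the order of entry, not over training level. With 58 students, one arm can by chance receive noticeably more of the advanced students. An unadjusted t-test on the competence score would then carry that difference in its estimate. Precision and the credibility of the comparison would suffer in a small trial, although the imbalance could be nearly ruled out in advance.

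**Working it through.** The protocol article gives no figure for semester balance, so there is none to reproduce. The check asks how large a chance imbalance the stated design permits, and what it could do to the primary comparison.

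**Inputs from the document**
- 58 students (Data collection, quantitative phase), allocated 1:1 (Randomization), so 29 per arm.
- No stratification factor (Randomization).

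**Assumptions, because the document is silent**
- Semester split: 50:50, that is 29 of 58 in the eighth semester. Range: 17 of 58 to 41 of 58, about 30:70 to 70:30.
- Competence difference between semesters: 0.3 to 1 SD.

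**Step 1. Distribution of the imbalance.** Let X be the number of eighth-semester students in the intervention arm, N = 58, K the eighth-semester total and n = 29. X is hypergeometric. The difference in semester share between the arms is d = X/29 − (K − X)/29 = (2X − K)/29.

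**Step 2. Typical size.** Var(X) = n × (K/N) × (1 − K/N) × (N − n)/(N − 1). For K = 29 this is 29 × 0.5 × 0.5 × 29/57 = 3.69, so SD(X) = 1.92 and SD(d) = 2 × 1.92/29 = 0.13. For K = 17 or 41, SD(d) = 0.12.

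**Step 3. Tail probabilities.** For K = 29, |d| ≥ 0.20 requires |2X − 29| ≥ 5.8. As 2X − 29 is odd, this means at least 7, so X ≤ 11 or X ≥ 18.

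| Assumed split | P(≥ 15 points) | P(≥ 20 points) |
|---|---|---|
| 29 of 58 | 0.294 | 0.114 |
| 17 or 41 of 58 | 0.248 | 0.082 |

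A simulation of unstratified blocks of four over 58 students, 50:50, gave SD 0.13 and P(≥ 20 points) = 0.14. The probability is a little higher because 58 is not a multiple of 4. The cut final block can leave arms of 30 and 28, where X = 18 in the larger arm already gives 18/30 − 11/28 = 0.207.

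**Step 4. What stratifying achieves.** The same simulation with blocks of four run separately within each semester gave SD(d) of about 0.02, and no simulated allocation reached 10 points.

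**Step 5. Effect on the unadjusted comparison.** Shift = imbalance × semester effect.
- At 20 points: 0.20 × 0.3 = 0.06 SD, up to 0.20 × 1 = 0.20 SD.
- At 7/29 = 24.1 points, the smallest value above the threshold that arms of 29 can show: 0.07 to 0.24 SD.
- For comparison, the standard error of a difference in means with 29 per arm is √(2/29) = 0.26 SD.

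Even in these less favourable allocations the shift is below one standard error.

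**The case against.** The strongest reply is that nothing here is an error. Permuted blocks without strata are a valid design. Chance imbalance does not bias the estimate in expectation and is already covered by the test's error rate and the confidence interval. This stands in full.

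A second reply is that the plan already has a route to adjustment. ANCOVA is named and competence is measured at baseline, so the baseline score could absorb much of a semester difference. This stands in part. Adjusting for the starting score need not remove a difference in growth between semesters, and the plan leaves the t-test in place for continuous outcomes. That covariates are unnamed is not the complaint, since such a list is commonly left to an analysis plan.

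Third, the size rests on an assumed split and an assumed semester effect, neither of which the document supplies. That is so, and it is why ranges are given. The phrase about the two semesters could also describe one cohort followed through both. The qualitative phase's wording makes a mixed pool the likelier reading but does not settle it.

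Three stronger readings are tempting and not supported:
- A reader might infer that semester is the factor most directly tied to the primary outcome. The document says nothing of the kind, and the baseline competence score is closer to the outcome.
- A reader might infer that a scale ceiling worsens the problem. The article gives a four-point response scale, but no total-score range or distribution.
- A reader might apply the block list literally. "Five blocks of 4 pieces and 3 blocks of 3 pieces will be extracted randomly using WIN PEPI software" and "in each block of 3 students, 1 student will be in control and 2 will be in intervention group" give 5 × 4 + 3 × 3 = 29 places, split 16 to 13, and an imbalance of 20 points or more would then occur in about 27% of allocations. That larger figure results from a separate inconsistency with 58 students at 1:1, and it should not enlarge this point.

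**Conclusion.** The point holds as a small, nearly free improvement, not as a flaw that invalidates the trial. The stated scheme leaves semester to chance. Under an equal split with 29 per arm, the typical imbalance is about 13 percentage points, and about one allocation in nine reaches 20 points or more (8% near 30:70). A 20-point imbalance would move the unadjusted difference by 0.06 to 0.20 SD if the semesters differ by 0.3 to 1 SD, less once the baseline score is adjusted for. The conclusion assumes a mixed pool of the two semesters, the split shown and some true semester effect; with no such effect, the imbalance would not matter. Stratifying would not address the plan to run the control group first and the intervention group afterwards, which is a separate matter.

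**What to change.** In the Randomization section, specify two separate 1:1 permuted-block lists, one for seventh- and one for eighth-semester students, generated in the software already named. In the quantitative Data analysis section, make the ANCOVA of the competence score, with baseline competence score and semester as covariates, the primary analysis in place of the unadjusted t-test. The Study status section reports that sampling for the quantitative phase is under way. Where students are already allocated, keep the allocation and make only the ANCOVA change, fixing it before outcome data are examined. The cost is one more allocation list and one or two model terms, with no extra students. The baseline score is already planned, and semester is known from eligibility.
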